### Putative Moderators of treatment

Cardiovascular and inflammatory markers

### Adverse events

- Reported adverse events

### Additional post-randomisation (follow-up) measures

- Concomitant medications
- Withdrawals from follow up
- Treatment guess
- Dosing regime

## **1.8 Sample size estimation (including clinical significance)**

### Sample size

A total of 240 first episode psychosis patients will be recruited over a two-year period.

### Power calculation

Based on recently collected PANSS Total score in FEP patients collected as part of the Physical Health and Substance Use Measures in first episode Psychosis (PUMP) study (n = 190), the mean (and standard deviation) score was 58.1 (15.0) units. Based on the number of new cases presenting to FEP services and based on the annual counts of FEP patients recruited into similar studies, we predict that we will recruit 120 patients per year (i.e. 240 over two years).

The primary intention to treat (ITT) analyses will compare two equally sized treatment arms, treatment or placebo on the PANSS scale at 6 months post-randomisation. For the power analyses, we modelled two plausible scenarios. For the primary outcome (six-month follow-up), we assumed a 20% attrition proportion. After 20% attrition the sample size is 192, 96 in each trial arm).

Based on alpha = 0.05 and power = 80%, samples between 200 and 180 participants will be able to confidently detect mean PANSS total score group differences of between 6 and 6.3 units. This equates to a standardised effect of size of approximately 0.4 to 0.42. Considering

## DFEND

90% power with the same power assumptions, we will be able to detect mean PANSS total score group differences of between units 6.9 and 7.3 units (standardised effect size from 0.46 to 0.49).

We also wish to estimate the average treatment effect in those participants who meet the vitamin D threshold. We assume 60% of the FEP have vitamin D concentrations below 50 nmol/L. At 6 months after 20% attrition (sample now = 192) and 60% who meet the vitamin D threshold, this will result in a projected sample size of 115.

Based on  $\alpha = 0.05$  and power = 80%, samples between 120 and 100 participants will be able to confidently detect mean PANSS total score group differences of between 7.7 and 8.5 units. This equates to a standardised effect of size of approximately 0.52-0.57. Considering 90% power with the same power assumptions, we will be able to detect mean PANSS total score group differences of between 8.95 and 9.8 units (standardised effect size from 0.60 to 0.65).

### 1.9 Brief description of proposed analyses

Analyses will be carried out by the trial statistician. The trial statistician will remain blind until all analyses are completed. The analysis of the secondary outcome of blood sampling vitamin D concentrations at 6 months will be carried out after all other analyses are completed as there is a high expectation that mean concentration will be higher in the intervention group.

The primary analyses of efficacy will be based on the intention-to-treat sample, utilising all available follow-up data from all randomised participants. The significance level will be 5% (2-sided) for all specified main and secondary analyses with estimates and confidence intervals presented for all effects.

All descriptive analyses, recruitment rate, consent rate, loss to follow-up, departures from randomised treatment and the prevalence of serious adverse events will be reported post-randomisation and summarised by treatment arm over the course of the study. All causes of withdrawal from randomised treatment will be reported.

The main objective of the statistical analyses is to assess the effect of vitamin D supplementation on the primary outcome PANSS total Score at the 6-month follow-up time point. To this end linear mixed modelling (LMM) will be employed.

Treatment effects on secondary outcomes will be using generalized linear models allowing for non-normal data where necessary. Treatment arm, baseline measurement of the outcome and randomization stratifier (ethnicity) will be included as covariates.

Average treatment effects (ATE) with the FEP population will be estimated at 3 and 6 months for the primary outcome and at 6 months for all secondary. We will also estimate subpopulation (baseline vitamin D insufficient and sufficient) specific treatment effects for the primary outcome and all secondary outcomes, except for 25OHD blood concentration levels, by use of an interaction of baseline vitamin D insufficiency status with treatment group in the statistical models.

We expect there to be some missing data in the post-treatment outcomes variables. The LMM analyses are based on maximum likelihood and will provide valid inferences under a missing at random (MAR) missingness mechanism. We will explore predictors of missingness, if deemed suitable for adjustment we will include these as explanatory

DFEND

variables in the analyses. If post randomisation or unsuitable baseline variables are identified a Multiple Imputation [3] model will be considered instead.

Sensitivity analyses will be used to assess the robustness of conclusions to data missing not at random (MNAR) outcome data and to departures from randomised treatment in the manner of White and colleagues [4].

Data summaries and analyses will be carried out in Stata.

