#### Could low vitamin D impair recovery from first episode psychosis?

Previously, we proposed that first generation dark-skinned migrants exposed to both “social defeat” and hypovitaminosis D may be less able to buffer stress-related adverse brain outcomes (McGrath, 2010). In light of the neuroprotective properties of vitamin D (especially those related to dopaminergic pathways), and in light of the recent findings that vitamin D supplementation can slow the progression of dopamine-related neurodegenerative disorders like PD, we believe that there is now a strong case to examine whether vitamin D supplementation can optimize outcomes in first episode psychosis (FEP) (McGrath, 2010).

A recently published systematic review (based on seven studies) has confirmed that those with psychosis are significantly more likely to have low concentrations of vitamin D (BelvederiMurri et al., 2013). Crews et al., 2013 recently examined vitamin D status in a sample of 69 patients with FEP and 69 controls matched on age, sex and ethnicity. FEP patients had nearly a three-fold increased risk of vitamin D deficiency (OR= 2.99, 95% CI=1.33-6.74). In the FEP group, over a third (36.2%) had frank vitamin D deficiency (less than 25 nmol/L) while an additional 25% of FEP were classified as having vitamin D insufficiency (between 25 and 50 nmol/L). As pilot data for this application, we undertook a preliminary analysis of data currently being collected for the IMPACT study ([www.kcl.ac.uk/iop/depts/ps/research/clinicaltrials/IMPACT.aspx](http://www.kcl.ac.uk/iop/depts/ps/research/clinicaltrials/IMPACT.aspx)). Low vitamin D at baseline predicted poorer function ( $r=.327$ ,  $p=0.045$ ) and higher Calgary depression scores ( $r=.404$ ,  $p=0.012$ ) at 12 months. A significant relationship between baseline Vitamin D and 12 months PANSS did not persist once adjusted for age, sex, ethnicity and season of sampling, but mean vitamin D between baseline and 3 months tended towards an association with PANSS

total ( $r = -.356$ ,  $p = 0.063$ ) and negative ( $r = -.342$ ,  $p = 0.059$ ) scores at 12 months, and had a significant relationship with 12 month Depression ( $r = -.369$ ;  $p = 0.038$ ) and GAF ( $r = .491$ ,  $p = 0.002$ ).

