## 7.2 Laboratory Tests

All blood samples will be obtained by a trained phlebotomist.

Blood will be taken for 25OHD concentration at baseline and 6 months but this assay will not be performed until the trial is complete. This is to ensure that researchers and clinicians are blind to baseline vitamin D status and that the patients will be offered standard clinical treatment. Additionally there is clinical equipoise regarding vitamin D supplementation in this group (i.e. the uncertainty of the intervention's efficacy versus the potential that leaving participant's vitamin D deficient will cause harm). This strategy has been employed successfully by one of the investigators ([name]) elsewhere (Gaughran et al., 2007). At the end of the study, once all data is analysed we will inform the participant's respective clinical team and/or GP of their vitamin D levels at last testing, noting that it may be some time after that test. Appropriate recommendations for post-study vitamin supplementation will be made by patient's GP or clinical team. Once the study is complete, serum samples will be shipped to the funder (Stanley Medical Research Institute) as part of the funding agreement, in an anonymous format. The Biomedical Research Centre (BRC) will store this sample until it is ready to be shipped to America. Clinical markers for cardiometabolic and general health will be tested from the same bleed (and shared with the clinical team with the patient's permission), and samples stored to later test for immune/inflammatory markers. Safety tests include calcium and if indicated parathyroid hormone test.

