## **2.3 Characteristics of baseline vitamin D**

Baseline descriptions of levels of sun exposure and vitamin D supplementation will be summarised by baseline vitamin D level (sufficient vs insufficient as defined by baseline blood vitamin D concentration levels greater or less than 50 nmol/L). The association between these variables and blood vitamin D concentrations can be assessed using suitable statistical tests (chi—squared, Fisher’s Exact or T test).

- Levels of sun exposure, including type of clothing worn, levels of physical activity (IPAQ), skin type (Fitzpatrick Skin Type questionnaire), vitamin D food frequency questionnaire, level of vitamin D supplementation, season of randomisation.

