### **Mechanism of action**

The study is based on the theoretical model that vitamin D supplementation might improve psychotic symptoms (PANSS) by increasing blood vitamin D levels to sufficient levels. We wish to investigate this empirically by partitioning any detected vitamin D supplement effect on PANSS into two components: (a) A part that is mediated via changing blood concentration levels (indirect effect) and (b) a non-mediated part (direct effect). To this end we will employ appropriate mediation methods such as the product of coefficients method or linear structural equation models. These methods rely on the assumption that all confounders of the blood level – PANSS path have been measured and included in the models [6].

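### Season is in none of the SAP's named covariate sets, so the 6-month 25OHD estimate gives up precision and the mediation analysis leaves a plausible confounder unnamed

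*Combined protocol and SAP*

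**What the plan says.** Sampling: protocol 7.2 states "Blood will be taken for 25OHD concentration at baseline and 6 months", and the assay waits until the trial is complete. The 6-month visit has a window of -4/+6 weeks (SAP 1.6), and the study runs from December 2015 to December 2019 (SAP 1.4), so entry falls in every season.

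Models: for secondary outcomes SAP 1.9 specifies "Treatment arm, baseline measurement of the outcome and randomization stratifier (ethnicity) will be included as covariates". The primary model in SAP 3.1.1 adds time and its interaction with arm, and adjusts for baseline PANSS and ethnicity. Neither names season.

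Season: SAP 2.3 lists "level of vitamin D supplementation, season of randomisation" among the characteristics to be summarised by baseline vitamin D group, with optional association tests. SAP section D records that season was once a randomisation stratifier.

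Mediation: SAP 3.1.2 says its methods assume that "all confounders of the blood level – PANSS path have been measured and included in the models". It lists no confounders.

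Pilot data: protocol section 3 reports that the link between baseline vitamin D and 12-month PANSS "did not persist once adjusted for age, sex, ethnicity and season of sampling".

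**The concern.** Protocol section 3 explains that vitamin D is made in the skin under UVB, so 25OHD can be expected to follow the calendar. With two samples about half a year apart, someone sampled in winter at baseline is usually sampled in summer at the endpoint, and the reverse. Two things follow.

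- **25OHD endpoint.** Season pushes the two values in opposite directions. Baseline 25OHD therefore predicts 6-month 25OHD less well than it could, and the seasonal swing stays in the residual.
- **Mediation.** If symptoms also vary through the year, season of the 6-month visit is a common cause of 25OHD and PANSS. Left out, it can look like an effect of blood level on symptoms. SAP 1.7 hopes to attribute any PANSS change to blood concentration, so a spurious path would bear on the trial's explanation of its result.

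The SAP's own reasoning points the same way. Ethnicity became a stratifier because blood vitamin D differs by ethnicity and is the hypothesised mediator (SAP 1.3), and SAP 3.1.3 then requires it in the models. The same argument applies to season.

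**Working it through.** **The plan's own figure.** SAP 1.8 says "samples between 200 and 180 participants will be able to confidently detect mean PANSS total score group differences of between 6 and 6.3 units", with alpha from "The significance level will be 5% (2-sided) for all specified main and secondary analyses" and SD from "the mean (and standard deviation) score was 58.1 (15.0) units". Detectable difference = (1.960 + 0.842) × 15 × √(4/N). This gives 5.94 at N = 200 and 6.26 at N = 180 (5.97 and 6.30 by t-test). The figure reproduces, and about 6 points is the yardstick below. No such calculation exists for 25OHD.

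**Assumptions (not in the documents).** Sinusoidal season of amplitude A, entry spread evenly over the year, samples exactly six months apart, equal seasonality in both arms, and within-person correlation r = 0.7 after removing season. Let V be the total variance, S = A²/2, T = V − S and C = rT − S (the baseline-endpoint covariance).

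- Residual variance without season: R = V − C²/V
- Residual variance with season: T(1 − r²)

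**Spread 1: SD 25 (V = 625).**
- A = 10: S = 50, T = 575, C = 352.5. R = 426.2; with season 575 × 0.51 = 293.3. Cut 31%.
- A = 20: S = 200, T = 425, C = 97.5. R = 609.8; with season 216.8. Cut 64%.

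Simulating the -4/+6 week window reduces these to about 29% and 60%.

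**Spread 2: fitted to protocol section 3.** There 36.2% are below 25 nmol/L and a further 25% are between 25 and 50, so 61.2% are below 50. A normal fit gives SD = 25/(0.285 + 0.353) ≈ 39 and mean ≈ 39, hence V = 1521. Take A as 15-35% of the mean, i.e. 5.85 to 13.65.
- A = 5.85: R = 815.9; with season 767.0. Cut 6%.
- A = 13.65: R = 980.9; with season 728.2. Cut 26%.

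Separate simulations of this scenario gave 5-23% and 6-25%.

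**Spread 3: little within-person noise** (between-person SD 20, within-person SD 8). For A = 5 to 20 the simulated cut is 24-76%.

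**What this means for the arm difference.** SE = √(2 × residual variance/96), with 96 per arm as in SAP 1.8.

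| Spread | A | SE without season | SE with season |
|---|---|---|---|
| 1 | 10 | 2.98 | 2.47 |
| 1 | 20 | 3.56 | 2.13 |
| 2 | 5.85 | 4.12 | 4.00 |
| 2 | 13.65 | 4.52 | 3.89 |

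Even the largest SE gives a detectable difference of 2.80 × 4.52 = 12.7 nmol/L at 80% power. The estimated arm difference is the same on average with or without season.

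**Mediation.** Assume no vitamin D effect on PANSS, a 40 nmol/L arm difference, PANSS worst in winter with seasonal amplitude P, and baseline 25OHD in the model. With s = C/V, the spurious indirect effect is −40 × (A·P/2) × (1 + s)/R.

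| Spread | A | P = 0 | P = 1 | P = 3 |
|---|---|---|---|---|
| 1 | 10 | 0 | −0.73 | −2.20 |
| 1 | 20 | 0 | −0.76 | −2.27 |
| 2 | 5.85 | 0 | −0.24 | −0.72 |
| 2 | 13.65 | 0 | −0.44 | −1.33 |
| 3 | 10 | 0 | −1.22 | −3.66 |

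Example, first row, P = 1: −40 × 5 × 1.564/426.2 = −0.73. Simulations gave −0.7 to −2.4 for spread 1 and −1.19 and −3.62 for the last row. With season terms the indirect effect returns to about zero, and the total randomised effect is about zero throughout. If baseline 25OHD is left out, spread 1 gives −40 × (A·P/2)/625, i.e. −0.32 to −1.92.

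**The case against.** The case against is strong on several points, and most of it limits what can be claimed.

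- **Bias in a randomised comparison.** A reader might infer that omitting season biases the treatment effects. It does not: randomisation balances season in expectation, and the subgroup label is fixed before allocation.
- **Missing the 25OHD effect.** A reader might fear that it goes undetected. SAP 1.9 expects a clear rise, and a difference of the assumed 40 nmol/L is more than three times the largest detectable difference above (12.7). Only the width of the interval is at stake.
- **Mediation already confounded.** The documents do not show this. It needs PANSS to vary by season, for which they give no figure. SAP 3.1.2 acknowledges that confounders must be included, and sun exposure is recorded at baseline and 6 months. What stands is that the confounder set is unspecified and season is not named in it.
- **Season in no model at all.** That also goes too far. It could still enter as a predictor of missingness (SAP 3.1.3) or as a mediation confounder. It is absent from the named sets.
- **The pilot.** It adjusted jointly for age, sex, ethnicity and season, so the lost association cannot be credited to season.
- **The 50 nmol/L subgroup.** A reader might call the label wrong because it depends on the month of entry. Under assumed amplitudes of 5-20 it would differ from annual-mean status in 4-22% of participants. But SAP 3.1.1 defines the subgroup by measured baseline concentration; annual-mean status is a different question. Crossings of 50 nmol/L over six months are not all seasonal either: at mean 45, SD 25, r = 0.7 and no seasonality, 21% of those below and 29% of those above would cross. Adding season as a main effect would not change the label.
- **The remedy.** Additive terms assume equal seasonality in both arms, which supplementation could blunt, and baseline date only approximates endpoint season. Both are fair; the first can be tested and the second costs little precision.

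**Conclusion.** The point holds in a limited form. No named covariate set includes season, although the sampling scheme makes season a predictable source of variation in 25OHD and the investigators' pilot analysis adjusted for it. Under assumed amplitudes, season terms would cut the residual variance of 6-month 25OHD by about 5-25% with the spread fitted to the protocol's prevalence figures and by about 30-60% at SD 25; only the low within-person-noise scenario goes higher.

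For mediation the effect is conditional. It is zero if PANSS does not vary by season. With a 1-3 point seasonal amplitude it is about -0.2 to -2.4 points in most scenarios and up to about -3.6 in the least favourable, i.e. at most 40% (2.4/6) or 60% (3.6/6) of the 6-point target. The sign assumes that symptoms are worse in winter and would reverse otherwise.

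All amplitudes, the 40 nmol/L contrast and the within-person correlation are assumptions. The primary PANSS conclusion is not affected.

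**What to change.** Amend the SAP before the 25OHD assay is run:

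1. **25OHD model (SAP 1.9 and 3.1.2).** Add sine and cosine of the calendar date of the baseline sample. This date precedes randomisation, so it is a safe covariate.
2. **Mediation (SAP 3.1.2).** List the confounders of the 25OHD-PANSS path, and include sine and cosine of the date of the 6-month sample among them.
3. **Check.** Fit an arm-by-season term once in the 25OHD model to test whether seasonality is similar in the two arms.
4. **Leave unchanged** the primary PANSS model and the 50 nmol/L subgroup definition. A subgroup analysis with season-standardised baseline 25OHD is an optional sensitivity analysis, labelled as a different question.

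The cost is SAP wording and two degrees of freedom per model. The dates should already be held: protocol section 13 includes blood-taking logs in the source notes, and SAP 3.1.3 already plans to summarise departures from planned time points. Because no 25OHD result exists until the trial is complete, terms added now are clearly prespecified; added later, they could look data-driven.

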## **2. *Data analysis plan – Data description***

### **2.1 Recruitment and representativeness of recruited patients**

A CONSORT flow chart will be constructed [2]– see Figure 2. This will include the number of eligible patients, number of patients agreeing to enter the trial, number of patients refusing, then by treatment arm: the number of patients not / inadequately / adequately treated OR compliant / non-compliant, the number continuing through the trial, the number withdrawing, the number lost to follow-up and the numbers excluded / analysed.

Figure 2. Template CONSORT diagram for DFEND trial

[figure not shown]

## **2.2 Baseline comparability of randomised groups**

Baseline descriptions of participants by treatment and overall: means and standard deviation, medians and upper and lower quartiles, or numbers and proportions will be reported as appropriate.

No significance testing will be used to test baseline difference between the randomised treatment groups [5].

The following baseline variables will be described both overall and between randomised groups:

1. Stratifications factors (ethnicity) and sociodemographics
2. Biomedical status will be measured as: waist circumference, weight, height (for BMI), blood pressure, heart rate (pulse), along with blood measures of cardiovascular risk / inflammatory markers and smoking habits.
3. Mental health status: The Positive and Negative Syndrome Scale (PANSS); Global Assessment of Functioning (GAF); Calgary Depression Scale (CDS).
4. Levels of sun exposure, including type of clothing worn, levels of physical activity (IPAQ), skin type (Fitzpatrick Skin Type questionnaire), level of vitamin D supplementation, vitamin D food frequency questionnaire.

## **2.3 Characteristics of baseline vitamin D**

Baseline descriptions of levels of sun exposure and vitamin D supplementation will be summarised by baseline vitamin D level (sufficient vs insufficient as defined by baseline blood vitamin D concentration levels greater or less than 50 nmol/L). The association between these variables and blood vitamin D concentrations can be assessed using suitable statistical tests (chi—squared, Fisher’s Exact or T test).

- Levels of sun exposure, including type of clothing worn, levels of physical activity (IPAQ), skin type (Fitzpatrick Skin Type questionnaire), vitamin D food frequency questionnaire, level of vitamin D supplementation, season of randomisation.

## **2.4 Adherence to allocated treatment and treatment fidelity**

Adherence to the oral study medication can be ascertained via the dosing schedule.

The numbers and proportions of participants in each of the treatment arms who were given the treatment that they were randomised to will be described. Adherence, including number of doses received will also be described.

## **2.5 Loss to follow-up and other missing data**

It is the aim of the trial to minimise withdrawal of participants from treatment and follow-up. Completion of a withdrawal from trial is regarded as withdrawal from follow-up in this analysis.

Withdrawal from trial will be reported by intervention group. Moreover, the proportions of participants missing each variable will be summarised in each arm and at each time point.

